## 2. Materials and Methods

### 2.1. Objective and Hypothesis

Our objective is to characterize quantitative hormones in the urine using the Mira monitor and validate these in reference to serum hormonal measurements and the gold standard of the ultrasound day of ovulation in participants with normal (regular) menstrual cycles. This will also help to establish external validity for the Mira monitor for use in women with regular cycles, rather than relying on industry-based internal data. We will then compare those with regular cycles to oligomenorrheic women with polycystic ovarian syndrome (PCOS) and oligomenorrheic athletes.

We hypothesize that the Mira monitor’s detected urine hormone pattern will accurately correlate with serum hormonal levels and will predict (LH) and confirm (PDG) the ultrasound day of ovulation in those with regular cycles as well as those with oligomenorrheic cycles.

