### 2.4. Recruitment and Sample Size Considerations

Recruitment will occur through the University of Calgary social media and research sites. We anticipate that a snowball sampling effect will also occur. Interested participants will be contacted by a research assistant to complete an online survey to ensure they meet the inclusion criteria (Table 1 and Table 2).

Previous ultrasound studies validating urine hormone monitor measurements have targeted 50 participants over 3 cycles, for a total of 150 menstrual cycles [41]. With 150 cycles for analysis, the study would be adequately powered to detect differences of 0.5 days in the estimated day of ovulation, cycle length, and follicular/luteal phase lengths. This calculation was done with G*Power 3.1, with an effect size of 0.2, alpha 0.05, and power of 80%. This calculation is valid for correlation statistics with an a priori power analysis with one tail. Oversampling up to 60 participants may be required to ensure that we have 150 cycles for analysis. The same sample size will be used for recruitment of the PCOS and athlete groups. We know that the participant burden is high, and therefore, we are prepared to continue to recruit until we reach sample size.

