## 3. Results (Planned)

### 3.1. Data Analysis

Datasets will be analyzed using SPSS version 29 (IBM, Chicago, IL, USA) and charts prepared using SPSS or Excel (Microsoft, Redmond, WA, USA). Descriptive statistics will be used to determine the means, standard deviations (SD), and 95% confidence intervals (CI) of the menstrual cycle parameters, i.e., cycle length, day of ovulation, length of the follicular phase and the luteal phase, menstrual bleeding scores, and duration. The ultrasound-defined day of ovulation (US-DO) will be considered day 0 as a reference for days leading up to and after ovulation. The main analysis in this sample (for which it is powered) will be to correlate (with Spearman’s correlation coefficients) the day of ovulation with peak levels of LH on the Mira monitor, as well as with the day of progesterone elevation, to confirm ovulation. Sensitivity and specificity analyses of each hormone in relation to the US-DO will be calculated.

Secondary exploratory data analyses (not considered in the power calculations) will include daily average hormone values from the Mira monitor referenced to day 0 (US-DO), average hormone values, 95% confidence individuals on days leading up to ovulation (days −5, −4, −3, −2, −1, etc.), and after ovulation (days +1, +2, +3, +4, +5 etc.) from cycle day 6 until the end of the cycle. Daily means, SDs, and CIs of hormone values across the study sample will be used to describe the variability in the population, as was done in the pilot study [34], and individual (personalized) hormone patterns will also be considered as we have presented in previous studies [51]. Day-to-day hormone variability will require complex modelling of hormonal patterns, which we have used in previous studies [53], using *R*-software (*R* Foundation for Statistical Computing, Vienna, Austria). The specific statistical methods involve creating best-fit distributions for wave patterns of the hormones using the mean square of residuals as the loss function, with the goal to minimize the loss function to improve the fit of the distribution based on the density of the hormone wave patterns in the population; this specific method has helped to identify distinct hormone patterns that may represent different physiologic mechanisms, but it must be emphasized that these are hypothesis-generating rather than primary endpoints of this proposal.

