**Figure 3 medicina-59-01513-f003:**
[figure not shown]
Data collection process for the study. Mira monitor urine results and other menstrual cycle observations are recorded in the Read Your Body (RYB) App. Users collect, control, and own the data they collect. RYB data is stored locally. Participants can then voluntarily send their anonymous data to a REDCap research database. Component figures used with permission.

**Table 1 medicina-59-01513-t001:** Inclusion and exclusion criteria for regular cycles.

Inclusion Criteria	Exclusion Criteria
Regularly menstruating participants aged 18–45 Consistent cycle lengths between 24–38 days Knowledge of previous 3 cycle lengths Negative pregnancy test at the beginning and at the end of each cycle Able to travel to clinic in Calgary for regular ultrasounds during the study period	Anovulation in the last 3 cycles Currently, or in the previous 3 months, on medications that are known to impair or stimulate ovulation (e.g., oral contraceptives, ovulation stimulants, etc.) Known conditions that impair ovulation or fertility: ▪ polycystic ovarian syndrome ▪ endometriosis ▪ pelvic inflammatory disease in the last year ▪ pituitary adenoma ▪ breastfeeding Previous surgeries impacting the menstrual cycle: ▪ hysterectomy ▪ bilateral oophorectomy Currently pregnant

**Table 2 medicina-59-01513-t002:** Inclusion and exclusion criteria for oligomenorrheic cycles.

Inclusion Criteria	Exclusion Criteria
Participants aged 18–45 With a clinical diagnosis of PCOS (Rotterdam criteria [45] to include oligomenorrheic cycles and one of either polycystic ovaries or signs of excess androgens) OR Oligomenorrheic athletes	Currently, or in the previous 3 months, on medications that are known to impair or stimulate ovulation (e.g., oral contraceptives, ovulation stimulants, etc.) Known conditions that impair ovulation or fertility: ▪ pelvic inflammatory disease in the last year ▪ pituitary adenoma ▪ breastfeeding Previous surgeries impacting the menstrual cycle: ▪ hysterectomy ▪ bilateral oophorectomy Currently pregnant

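### Accuracy is measured only against the ultrasound date of ovulation, so false PDG confirmations and false LH surges in cycles without ovulation are not counted

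*Protocol article*

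**What the plan says.** Section 3.1 fixes the reference standard as a date: "The ultrasound-defined day of ovulation (US-DO) will be considered day 0 as a reference for days leading up to and after ovulation". The main analysis is a Spearman correlation of "the day of ovulation with peak levels of LH on the Mira monitor, as well as with the day of progesterone elevation, to confirm ovulation". The accuracy analysis follows in one sentence: "Sensitivity and specificity analyses of each hormone in relation to the US-DO will be calculated".

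The hypothesis in section 2.1 is that the monitor "will predict (LH) and confirm (PDG) the ultrasound day of ovulation in those with regular cycles as well as those with oligomenorrheic cycles".

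On who supplies the cycles:

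- Table 1 (Group 1) requires "Consistent cycle lengths between 24–38 days" and lists as an exclusion "Anovulation in the last 3 cycles".
- Table 2 (Groups 2 and 3) has no such exclusion. PCOS is defined by "Rotterdam criteria [45] to include oligomenorrheic cycles and one of either polycystic ovaries or signs of excess androgens", and athletes must be oligomenorrheic.
- Section 1.1 associates long, irregular, anovulatory cycles with PCOS and says athletes have similar disturbances. It gives no rate of anovulation.
- Section 2.4 sets 150 cycles for Group 1 and adds: "The same sample size will be used for recruitment of the PCOS and athlete groups".
- Section 2.9 plans about 6 to 8 scans per cycle.

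**The concern.** A test that confirms ovulation can fail in two ways: it can miss an ovulation, or it can confirm one that did not happen. The second error shows most plainly in cycles without ovulation, and these are the cycles to which a date-based reference gives no value. They drop out of the correlation because there is no day to correlate. They have no place in an accuracy analysis defined relative to that day either.

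At stake is the confirmation claim in the irregular groups. Section 4.4 looks forward to relying on such monitors without ultrasound in every study. In PCOS and in athletes, that reliance depends on how often PDG rises, or LH surges, when no ovulation occurs. The analysis as worded could report good accuracy and leave that question open.

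A second problem is that specificity for one target day per cycle is high by construction, because nearly every day is a true negative.

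**Working it through.** **The plan's own figure.** Section 2.4 gives 150 cycles for effect size 0.2, one-tailed alpha 0.05 and power 80%, for a correlation. With r = 0.2 and cycles treated as independent, the noncentral-t correlation model gives n = 150. The Fisher z formula, ((z₀.₉₅ + z₀.₈₀)/atanh(0.2))² + 3, gives 153.4, so 154. The figure reproduces. It powers a correlation, and no precision is stated for sensitivity or specificity.

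**Single-day call (LH peak), days as the unit.** The cycle length L is 24 to 38 days (Table 1); 28 is used as an illustration. One day is positive (US-DO) and L − 1 are negative. A flag that is always on a wrong day makes one false positive per cycle, so specificity = (L − 2)/(L − 1) and sensitivity = 0.

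| L | Always-wrong flag | Random flag: specificity 1 − 1/L | Random flag: sensitivity 1/L |
|---|---|---|---|
| 24 | 22/23 = 95.7% | 95.8% | 4.2% |
| 28 | 26/27 = 96.3% | 96.4% | 3.6% |
| 38 | 36/37 = 97.3% | 97.4% | 2.6% |

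If the days within one day of US-DO also count as positive, an always-wrong flag has specificity (L − 4)/(L − 3): 95.2%, 96.0% and 97.1%.

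**PDG read as a state (ovulation has passed), within ovulatory cycles.** Days up to and including US-DO are the negatives; call their number p. For a rise on a random day, mean specificity = 1 − (p + 1)/(2L). Luteal lengths of 11 and 14 days are assumed.

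- L = 24, p = 10: 1 − 11/48 = 77.1%
- L = 24, p = 13: 1 − 14/48 = 70.8%
- L = 28, p = 14: 1 − 15/56 = 73.2%
- L = 38, p = 24: 1 − 25/76 = 67.1%
- L = 38, p = 27: 1 − 28/76 = 63.2%

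A rise three days too early gives 1 − 3/p, from 70% (p = 10) to 89% (p = 27). This measure separates good from bad performance.

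**Cycle-level specificity, anovulatory cycles as negatives.** The documents give no anovulation rate, so the shares below are assumptions applied to 150 cycles. Intervals are exact (Clopper–Pearson) and treat cycles as independent. When all k negatives are classified correctly, the lower 95% limit is 0.025^(1/k).

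| Assumed share | Negative cycles | Result | 95% interval |
|---|---|---|---|
| 0% | 0 | undefined | – |
| 2% | 3 | 3/3 correct | 29–100% |
| 5% | 8 | 8/8 correct | 63–100% |
| 10% | 15 | 15/15 correct | 78–100% |
| 20% | 30 | 27/30 correct | 74–98% |
| 40% | 60 | 54/60 correct | 80–96% |
| 60% | 90 | 81/90 correct | 82–95% |

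With 5 negatives, all correct, the lower limit is 0.025^(1/5) = 47.8%. The low shares are plausible for a group screened as in Table 1. The higher shares illustrate Groups 2 and 3.

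**The case against.** The strongest reply is that the accuracy sentence is brief and fixes no unit, window or negative class. An article commonly leaves such details to a fuller document, and nothing says that cycles without a US-DO are discarded. That is fair as to the details, and their absence is not the point made here. What the article does fix is the reference itself. It is a date, and a date cannot serve an anovulatory cycle.

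Three stronger readings are tempting, and the documents do not support them.

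- *That confirmation of ovulation cannot be tested at all.* The Table 1 exclusion concerns history at entry, so anovulatory cycles can still occur in Group 1 during the study. Table 2 does not exclude anovulation. Serial scans could identify cycles without ovulation. The hypothesis also has a timing component, which can be tested in ovulatory cycles by counting a PDG rise before US-DO as a false positive.
- *That PDG specificity is trivially high.* This holds for single-day calls only. With pre-ovulatory days as negatives, a random PDG rise scores about 63% to 77%.
- *That the irregular groups lose power.* If half of 150 cycles had no US-DO, 75 would remain and one-sided power at r = 0.2 would be 53% instead of 79%. But sections 2.4 and 3.2 set the target in analysable cycles, and section 2.4 is prepared to keep recruiting until it is met. The loss needs both an assumed anovulation share and a stopping point that the plan does not state.

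It also stands that 6 to 8 scans may not establish absence of ovulation throughout a long oligomenorrheic cycle, and that up to three cycles per woman make independent-cycle intervals potentially too narrow. The fix allows for both.

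**Conclusion.** The concern holds in a limited form. Measured in relation to US-DO, the accuracy analysis has no place for anovulatory cycles. False PDG confirmations and false LH surges in those cycles are therefore not counted, although the hypothesis extends to oligomenorrheic cycles.

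For a single-day call such as the LH peak, day-level specificity of about 96% to 97% is reached by a flag that is never right, so such a figure should not be offered as evidence of accuracy. This rests only on the 24- to 38-day range in Table 1.

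Cycle-level specificity is undefined or very imprecise in Group 1 if few cycles are anovulatory. It can be estimated in Groups 2 and 3 under assumed shares of 20% to 60%. Those shares, and the luteal lengths used for PDG, are assumptions. The size of the bias from omitting anovulatory cycles cannot be calculated from the documents. The point should be addressed, but it does not undermine the main correlation analysis.

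**What to change.** In section 3.1, or in the analysis plan it relies on:

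1. Add a cycle-level reference, ovulation on ultrasound yes or no, with an indeterminate class where the scans do not settle it. Keep US-DO for timing.
2. Keep anovulatory cycles of all three groups in the accuracy analysis as negatives.
3. Report PDG-confirmation sensitivity in ovulatory cycles and specificity in anovulatory cycles, mainly from Groups 2 and 3, with intervals that allow for repeated cycles per woman.
4. Within ovulatory cycles, report PDG rises before US-DO as false positives.
5. For LH, replace single-day specificity with timing agreement with US-DO within a stated window, plus false surges per anovulatory cycle.

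The cost is modest: a little more analysis work, no added procedure, and the number of indeterminate cycles to report, probably most among long cycles. Specificity for Group 1 alone will be imprecise and should be shown with its interval.

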### 3.3. Anticipated Results

We expect that the Mira monitor will accurately and precisely identify and confirm the day of ovulation as shown on ultrasound. Bleeding patterns and menstrual cycle observations will provide a baseline pattern for normal healthy participants to compare to abnormal cycles. We may be able to further expand on previous work related to daily quantitative hormone patterns, for example, by modelling estrogen changes from follicular wave activity in the early follicular phase [56], demonstrating the diversity of LH profiles related to ovulation patterns [57], or showing luteal progesterone variability [52,58]. The results from this study will potentially provide nomograms for urinary hormone measurements and provide reference values for future studies evaluating menstrual health.

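### Hormone curves averaged by day from ultrasound ovulation to the end of each cycle rest, at both tails, on a shrinking set of cycles selected for long follicular or long luteal phases

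*Protocol article*

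**What the plan says.** Section 3.1 fixes the alignment: "The ultrasound-defined day of ovulation (US-DO) will be considered day 0 as a reference for days leading up to and after ovulation". It fixes the span in the same section: averages are given for days before ovulation and "after ovulation (days +1, +2, +3, +4, +5 etc.) from cycle day 6 until the end of the cycle". The summary on each day is also stated: "Daily means, SDs, and CIs of hormone values across the study sample will be used to describe the variability in the population".

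The status is clear: "Secondary exploratory data analyses (not considered in the power calculations) will include daily average hormone values from the Mira monitor referenced to day 0". The same section also plans individual hormone patterns and a separate modelling of hormone waves, described as hypothesis-generating.

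Table 1 admits to the regular group participants with "Consistent cycle lengths between 24–38 days". Section 3.3 hopes that the results will "potentially provide nomograms for urinary hormone measurements and provide reference values for future studies evaluating menstrual health".

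The article states no limit on the range of aligned days, no minimum number of cycles per day and no second alignment for the two ends of the cycle.

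**The concern.** Cycles aligned on a single point overlap fully only near that point. Away from it, the mean on a given day is taken over those cycles that are long enough on that side, so the set of cycles changes from day to day along the curve.

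Before ovulation, a cycle reaches a distant day only if its follicular phase is long. After ovulation, it reaches a distant day only if its luteal phase is long. The loss on the luteal side is also tied to the hormone being averaged: a cycle leaves when menses starts, which follows its fall in PDG. The cycles that remain are those whose PDG has not yet fallen as far. A confidence interval computed from the remaining cycles does not show this.

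At stake is the use of the tails as reference values. A late-luteal PDG curve that falls more slowly than individual cycles do, or an early-follicular curve drawn from long follicular phases, would be a poor standard for judging a single patient's cycle. Section 3.3 itself names early-follicular estrogen and luteal progesterone variability as areas it hopes to expand on.

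**Working it through.** **The plan's own figure.** Section 2.4 cites a precedent of "50 participants over 3 cycles, for a total of 150 menstrual cycles" and adopts 150 cycles. With r = 0.2, one-sided alpha 0.05 and 80% power, the point-biserial model gives N = 150 (power 0.8006); Fisher's z gives 153.4, rounded up to 154. The figure reproduces. It belongs to the primary correlation and has no bearing on the daily curves.

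**Inputs from the documents.** Day 0 is the ultrasound day of ovulation; values start on cycle day 6 and run to the end of the cycle (Section 3.1); cycle length is 24–38 days (Table 1).

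**Assumptions.** Cycle length L ~ N(29, 3) limited to 24–38; luteal length l ~ N(13, 2), independent of L; both in whole days. Ovulation falls on cycle day L − l.

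**Rule.** A cycle contributes to day −k if L − l − k ≥ 6, and to day +k if l ≥ k.

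**Single cycles, 13-day luteal phase.**
- L = 24: ovulation on day 11, first contributing day 6 − 11 = −5.
- L = 38: ovulation on day 25, first contributing day 6 − 25 = −19.

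The starting points differ by 38 − 24 = 14 days, whatever common luteal length is assumed.

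**Luteal side.** In whole days the share at +k is P(Z ≥ (k − 0.5 − 13)/2).
- +10: P(Z ≥ −1.75) = 96%
- +12: P(Z ≥ −0.75) = 77%
- +13: P(Z ≥ −0.25) = 60%
- +14: P(Z ≥ 0.25) = 40%
- +15: P(Z ≥ 0.75) = 23%

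With a luteal SD of 1.5 to 2.5, the share at +13 is 63% to 58%. At +15 the contributors' mean luteal length is 15.7 days against 13.0 overall, while their mean total cycle length stays at 29.2.

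**Follicular side.** The condition is L − l ≥ 6 + k. Ignoring the 24–38 limit, L − l has mean 16 and SD √(9 + 4) = 3.61.
- −10: P(Z ≥ (15.5 − 16)/3.61) = P(Z ≥ −0.14) ≈ 56%; simulation with the limit gives 57%.
- −14: P(Z ≥ (19.5 − 16)/3.61) = P(Z ≥ 0.97) ≈ 17%; simulation also gives 17%.

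Simulation gives 96% at −5, 78% at −8 and 35% at −12. The contributors' mean cycle length rises from 29.2 overall to 30.8 at −10 and 32.8 at −14.

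**Other assumed lengths.** Three further settings were run, with follicular mean/SD 15/2.5, 16/3 and 17/4 and luteal 13/1.5, 13/2 and 12.5/2. Cycles contributing out of 150:

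| Day | Cycles |
|---|---|
| −5 | about 148 |
| −10 | 67–105 |
| −12 | 25–72 |
| −15 | 2–28 |
| +5 | 150 |
| +10 | 142–149 |
| +12 | 108–130 |
| +14 | 48–63 |
| +15 | 24–36 |

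**PDG illustration (shape assumed).** Let each cycle's PDG stand at its plateau (1.00) and fall by 0.18 per day over the last 5 days, so that it ends at 0.10. The contributors' values, from the shortest luteal length still present upward, are 0.10, 0.28, 0.46, 0.64, 0.82 and 1.00.
- Day +13: weights 0.197, 0.175, 0.121, 0.066, 0.028, 0.012 (sum 0.599). Weighted sum 0.201; mean 0.201/0.599 = 0.336.
- Day +14: weights 0.175, 0.121, 0.066, 0.028, 0.009, 0.003 (sum 0.401). Weighted sum 0.110; mean 0.110/0.401 = 0.274.

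The averaged curve falls by 0.336 − 0.274 = 0.062 from +13 to +14, about a third of the 0.18 within each cycle. Near day +10 it falls by about 0.12. For a linear 5-day fall, the ratio of a third is the same at any steepness; a different shape or luteal spread would change it.

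**The case against.** The strongest reply is that these curves are declared exploratory and outside the power calculation, that Section 3.3 speaks only of potential nomograms, and that ovulation is the natural anchor for a study validating ovulation timing. The days that Section 3.1 lists by number, −5 to +5, are nearly complete (96% at −5 and 100% at +5 in the main model). The section also plans individual patterns, so the mean curve is not the only description of shape. A condensed article may leave counts per day and cut-offs to a fuller document. All of this limits the weight of the point. It does not remove it, because the alignment and the span are written into the article: following them as stated produces the selected tails.

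Four stronger readings are tempting and not supported:
- That all days far from ovulation come only from long cycles. Before ovulation the shift is gradual: at day −8, 78% of cycles still contribute. After ovulation the selection is on luteal length. In the three further settings, 15% to 23% of the contributors at day +15 had cycles of 28 days or shorter.
- That differences between the regular, PCOS and athlete groups would be artefacts. Section 2.1 says that groups will be compared, but nothing states a day-by-day comparison on these curves.
- That the curves pool all three groups. The reference to the study sample leaves this open.
- That the main result is compromised. The correlation of ovulation day with the LH peak and the progesterone rise does not use the averaged tails.

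**Conclusion.** The point holds as an inexpensive improvement to a secondary analysis. As written, the daily means become means over selected cycles at both tails. Under the main assumptions coverage is about 90% or more from day −6 to day +10, then 57% at −10, 17% at −14, 60% at +13 and 40% at +14. The other assumed settings move these figures but keep the pattern.

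The existence of the selection follows from the stated alignment, the stated span and the 24–38 day range. Its size rests on assumed phase lengths, since the documents give none. The direction of the PDG distortion (an averaged fall flatter than the individual one) follows from cycles reaching menses on different days; its amount depends on the assumed PDG shape. The consequence is confined to the exploratory curves and to any nomograms or reference values taken from their ends.

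**What to change.** Amend the description of the daily curves in Section 3.1 as follows:

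1. Print the number of contributing cycles for each aligned day.
2. Offer ovulation-aligned means as reference values only for days with near-complete coverage, for example at least 90% of the ovulatory cycles in the group. The threshold is a convention and may be set differently, provided it is fixed in advance.
3. Summarise the late luteal phase on days counted back from the next menses, and the early follicular phase on cycle day.
4. If regular and irregular groups are compared on daily curves, make the comparison on these common scales.

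The cost is analysis wording. Section 3.1 already derives cycle length, day of ovulation and both phase lengths, so no further data are needed. The downside is an extra panel or two in place of one continuous curve, and fewer reported days at the ends.
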